
### Randomization and blinding

Sequence numbers of the patients with dementia will be generated by a computer-produced random list, which is performed by a statistical expert from Ningxia Medical University. But she is independent of the trial. The randomization schedule in a sealed envelope will be kept in a dedicated research office. There are many strategies to ensure the concealment of data distribution and minimize selection bias as well as create a double-blind environment. It will be blind to the randomized lists for participants (e.g., other researchers, patients, and caregivers) except the investigator responsible for conducting the intervention [24]. The project manager can suspend blinding until all the trials have been carried out according to the rules. The research team is responsible for reducing the rate of loss of intervention. Prior to the trial, the researcher went into the nursing home and lived and worked with the caregivers of the elderly to learn about the patient’s lifestyle. Meanwhile, they obtained their and their caregivers’ support and cooperation. Patients and their caregivers will be presented face to face with detailed information, which includes intervention process, collection and use of data and biological specimens, benefits, and potential adverse reactions from the trial [23]. But patients also have the right to withdraw from the study at any time without affecting subsequent care. In case patients and (or) their caregivers decide to quit the trials, data and biological specimens will be destroyed. It has been also documented in the informed consent form.

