## Methods

### Study design

This study is a multi-center and single-blind, randomized, sham-controlled clinical trial. It aims to compare and analyze the one-time analgesic effect between the intervention group and the sham-controlled group (Fig. 1, Table 1) for acute pain in patients with dementia. This trial, superiority framework, was designed on the basis of SPIRIT guidelines and the Consolidated Standards of Reporting Trials (CONSORT) statement [18, 19]. The Ningxia Medical University Ethics Committee has given its official approval for the study protocol, which has been registered at the Chinese Clinical Trial Registry (No.: ChiCTR2100047932). Each patient will be given a detailed explanation by the researcher including the purpose, benefits, and potential risks of the study. Moreover, they can withdraw from the study at any time, and this will not affect medical services other than the research. Subsequently, the qualified recruits who signed informed consent entering the study will receive APP or shamed APP treatment by an investigator, a master candidate in nursing science with APP professional training. It is needed to make important protocol modifications to reduce underpower of the study protocol and increase patient safety. We will communicate with the Data Management and Safety Monitoring Committee (DMSMC), all participants, and the Ethics Committee.

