**Fig. 1 Fig1:**
[figure not shown]
Study design framework. BP, blood pressure; HR, heart rate; SpO_2_, oxygen saturation; APP, auricular point acupressure; Score of pain, the Face Pain Scale Revised

**Table 1 Tab1:** Schedule of enrollment, interventions, and assessments

Procedure	Study period			
	Enrolment	Post-allocation		
	Dementia patients with acute pain	T0	T1	T2
Enrolment				
Eligibility screen	×			
Informed consent	×			
Allocation	×			
Interventions				
Control group			×	×
Treatment group			×	×
Assessments				
Face pain scale revised	×	×	×	×
Blood pressure		×	×	×
Oxygen saturation		×	×	×
Heart rate		×	×	×
Satisfaction				×
Acceptance				×
Side effect			×	×
Additional use of analgesics during the intervention				×

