### Management and safety monitoring

Prior to the study, research team members will receive a training program, which will cover the research design, procedure, evaluation of outcome measures, randomization, data collection, and data monitoring. For example, data recorders will be trained on how to collect and manage data to ensure the objectivity, quality, and safety of data as far as possible. Patients were anonymous throughout the trial. All subject’s personal information will also be stored in a separate envelope. It will then be saved in a Microsoft Access (Microsoft Office 2010, Redmond, WA, USA) database, which is password protected [23]. A separate code was generated by pre-randomization and kept by the project manager. It is a unique identifier that identifies anonymized data. With the consent of the project leader, only members of the research team have access to the collected information for a reasonable reason [24]. Another Microsoft Access database will be used to store all trial data. It can only be got by the data collectors, the investigator, and the DMSMC. It is necessary although the APP treatment was the least risky. It consisted of the project manager, principal researcher and physician of each sub-center, and experts from the Ethics Committee of Ningxia Medical University. They are primarily responsible for the quality control of clinical trials, including but not limited to the data collection and management and uniform training for investigators. Regular monitoring and auditing data will be also required. It should be also noted that the trained data collectors and investigators are fixed and that data quality control is carried out through double-entry bookkeeping by them [23, 24]. In addition, information on patients with withdrawal will not be included in the final analysis, and other researchers will investigate what led them to withdraw from the trial. According to previous studies, the side effects of this intervention have been reported rarely. Conducting an interim analysis or stopping rules will not be applied to the current study. All of the study subjects were elderly patients, so they will be closely monitored as part of the standard of care before, during, and after study participation.

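### The treating investigator is exempt from blinding to the whole randomisation list, T0 follows allocation, and the article calls the trial both single-blind and double-blind

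*Protocol article*

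**What the plan says.** Under Randomization and blinding, the protocol article has a statistical expert produce a computer-generated list, and says of that expert: "But she is independent of the trial". On storage it says: "The randomization schedule in a sealed envelope will be kept in a dedicated research office". The section claims that its measures conceal allocation, limit selection bias and "create a double-blind environment". It then states who is kept from the list and who is not: "It will be blind to the randomized lists for participants (e.g., other researchers, patients, and caregivers) except the investigator responsible for conducting the intervention".

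Under Study design the trial is described as a "multi-center and single-blind, randomized, sham-controlled clinical trial".

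Table 1 marks allocation in the enrolment column and puts T0, T1 and T2 under the heading "Post-allocation". The Measurement section names T0, taken before the intervention starts, as the baseline for pain score, blood pressure and heart rate. Table 1 also marks an FPS-R assessment at enrolment. The Primary outcome section gives the recording of pain to a researcher charged with that task.

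Under Management and safety monitoring, the article says of the trial database: "It can only be got by the data collectors, the investigator, and the DMSMC".

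**The concern.** A therapist has to learn each patient's arm in order to press the right points. A therapist does not need the sequence. Someone who can read the sequence knows what the next patient will receive before that patient is enrolled, and concealment exists to prevent exactly that. Entry here depends partly on a self-reported pain score of at least 4 on the FPS-R, which can vary over a short time. Foreknowledge could therefore affect who is enrolled and when.

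The order of allocation and baseline adds to this. The primary outcome is pain relief, and the named baseline is scored at a time when the arm may already be known to someone at the bedside. With a subjective outcome, readers will want to know who was blind to what, and the article gives two different labels.

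**Working it through.** No figure in the article bears on this point, so the check sets its sections against each other.

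1. **Scope of the exemption.** The blinding sentence concerns the lists. Other researchers, patients and caregivers are blind to them; the person conducting the intervention is the stated exception. The wording does not limit that exception to the patient being treated.

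2. **Concealment device.** The article describes one schedule in one sealed envelope held in a research office. It describes no release patient by patient. The independence of the list maker protects how the list is generated. It does not control who reads the list afterwards.

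3. **Consequence if followed as written.** Assume simple 1:1 randomisation (the article gives the ratio but no restriction). Under concealment the next assignment can be guessed with probability 0.5. A person who has the list knows it with probability 1.

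4. **Order of allocation and baseline.** Table 1 gives the order: enrolment FPS-R and allocation, then T0, then T1 and T2. The Measurement section makes T0, not the enrolment score, the baseline. If pain relief is taken as change from T0 (the article does not define the calculation), one part of the primary outcome is measured after the arm can be known.

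5. **Who scores pain.** A separate recorder is named for the primary outcome. That person falls among the blinded other researchers by implication; no sentence says so directly. T1 is scored 5 minutes into the procedure, while the unblinded therapist is at work.

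6. **Who sees the data.** Study design uses the word investigator for the person who treats. Management and safety monitoring uses the same word for one of those with database access, and has data collectors and investigators carry out the double entry. The article neither equates nor separates these people.

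7. **Labels.** Study design says single-blind; Randomization and blinding says double-blind. The people listed as blind are patients, caregivers and other researchers; the therapist is not. Naming these roles would remove the need for either label.

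Items 1, 2, 4 and 7 are stated text. Items 5 and 6 are points on which the text leaves the roles open.

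**The case against.** The strongest reply is that the language is loose and the article condensed. Being unblind to the lists may mean only that the therapist learns each arm at treatment, which cannot be avoided. The article does not say that the therapist holds the envelope or when it is opened, and envelope numbering is a detail usually left to a full protocol. This has force against any complaint about missing detail. It does not remove the point, which rests on a stated exemption that is wider than treatment requires.

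Several stronger readings are tempting and are not supported:

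- *The therapist screens patients, obtains consent or scores eligibility.* No section assigns these tasks to the therapist. The word researcher is used both for those who obtain consent and for the person who treats, so overlap is neither shown nor excluded.
- *The primary outcome is assessed unblinded.* A separate recorder is named, other researchers and patients are listed as blind, and patients must understand the FPS-R to be included. Assessor blinding is intended.
- *The unblinded therapist works in the outcome database.* This rests only on a shared word. Double entry is described as quality control, not as scoring.
- *The post-allocation T0 is itself a source of bias.* T0 still precedes treatment, and an FPS-R score is also taken at enrolment. If the recorder is effectively blind, the order matters little.

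It is also true that new envelopes cannot help patients already randomised. The article gives December 2021 as the expected end of recruitment and was published in May 2022, although it describes recruitment as ongoing.

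**Conclusion.** The concern stands in limited form. As written, the plan lets the treating investigator know upcoming assignments and places the baseline after allocation, so the claimed protection against selection bias is not secured. The single-blind and double-blind descriptions contradict each other and need correction whatever the actual practice.

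This conclusion assumes that the exemption is read literally. It does not assume that anyone has misused the list, that the outcome recorder is unblinded, or that the therapist has database access. The size of any bias cannot be estimated: the article gives no information on how many enrolments could be influenced or by how much, and any figure would depend wholly on invented inputs. The point is a cheap improvement to the design together with one plain inconsistency to correct.

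**What to change.** - For patients still to be randomised, have the independent statistician supply sequentially numbered, opaque, sealed envelopes, one per patient, or an equivalent one-at-a-time release. The therapist opens each only after consent, eligibility and all T0 values are recorded.
- In Table 1, move allocation to after T0.
- State that the therapist does not enrol patients, score the FPS-R, or enter or view outcome data before database lock.
- Describe blinding identically under Study design and under Randomization and blinding: patients, caregivers and outcome recorders blind, therapist not.
- For patients already randomised, report who had access to the list.

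The cost is stationery or a simple release system, database permissions and a few sentences; separate data collectors are already planned. The therapist waits briefly for T0 before opening the envelope. Patients already randomised cannot be repaired, so for them the remedy is disclosure. If recruitment has closed, the database restriction (until lock), the single description of blinding and the report on list access are what remain.

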### Measurement

Each patient’s demographic data (age, sex, nationality, educational background, marital status, occupation before retirement, personal income per month, history of taking medicine, chronic case history) will be recorded by a self-designed questionnaire. Other information including physiological parameters (heart rate, blood pressure, and oxygen saturation), sore spot, pain score, adverse effects, the use of analgesics in the intervention, satisfaction of caregivers, and acceptance of patients, will be more rigorously documented. The MoCA is made to identify the severity of dementia among the patient. And locality of the pain will be shown clearly according to the Brief Pain Inventory Chinese version (BPI-C) [25]. The FPS-R with great reliability and validity will be elected to assess pain intensity, and three physiological parameters are monitored with electronic sphygmomanometer (OMRON, HEM-7120) and Fingertip Oximeter (PC-60B). The data required for the study include pain score, noninvasive monitoring of blood pressure, heart rate collected at baseline (before performing the intervention, T0), at 5 min during performing the intervention (T1), and at 5 min after the intervention finished (T2) as well as digital monitoring of oxygen saturation. The intervention process of APP should be closely monitored, even if there are no reports of its side effects. And it will be recorded in detail and properly handled for any adverse reactions observed. The use of analgesics in the intervention also will be carefully recorded to enhance analysis of the safety and analgesic effect of APP. Satisfaction from caregivers will be surveyed via a 5-point satisfaction scale (5, very satisfied; 4, satisfied; 3, uncertain; 2, dissatisfied; 1, very dissatisfied) at T2 [26]. However, acceptance of patients will be measured by just asking them if they would like to accept the APP treatment once again.

### Outcome measurement

#### Primary outcome measure

The level of pain relief at T1 and T2 will be considered as the primary outcome. It is accurately recorded by a researcher in charge of recording on the basis of the FPS-R.

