### Interventions

The intervention group will be planned to receive auricular-plaster therapy, with one piece of Semen Vaccariae® (about 2 mm in diameter, Taicheng Technology and Development Co., Ltd., Shanghai, China) attaching to the center of a piece of medical adhesive tape (6 mm × 6 mm). This study initially selected four active acupoints including shenmen (TF4), subcortex (AT4), adrenal (TG2P), and two auricular points corresponding to pain sites based on the Nogier auricular point diagram for managing pain [22]. A researcher will bring the required items to the participants’ bedside and assist them in taking the position that is easy to operate. Subsequently, the researcher holds the helix with the left hand and identifies sensitive points by virtue of an ear probe with the right. The medical adhesive tapes with Semen Vaccariae® will be pasted on the selected auricular points with forceps by the researcher after checking and sterilizing the skin of the patients’ ears using 75% alcohol. Then, each auricular point will be pressed gently 2 times lasting 1 min each time. There is no time interval during the operation unless adverse reactions occur or until finishing the procedure. The pressure should be moderate and enough within individual’s endurance (the subject feels swelling pain, numb, and warm sensation). After the whole intervention, these tapes will be removed. However, these five points (kidney, CO10; ocuiput, AT3; internal ear, L06; external ear, TG1u; adrenal gland, TG2P) were selected in the control group. The main effect of these five points was to delay hearing loss; its procedures are described in the intervention group. However, the subject simply experiences the warm sensation in their ears. Relevant concomitant care is permitted during the trial. Although adverse reactions associated with auricular acupressure are rare, in this study, if they occurred (side effects occur during the implementation, they are short-lived and mild [15, 16]) or the participant’s requirements that the intervention they receive be discontinued, researchers can determine whether the trial will continue. Furthermore, the reasons for the withdrawal will be logged. Strategies to improve adherence to intervention protocols will be applied in *Trials*. Prior to the protocol, researchers will describe the method and duration of the intervention and the potential risk involved to the participants in detail [23]. In the intervention, there are many patients’ physiological parameters monitored by the data collector. A supervised compliance form (SAF) for this study protocol is necessary to collate patient compliance [23].

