### Sample size estimation

After obtaining the ethical approval of our study protocol, a preliminary experiment with a sample size of 30 was conducted in Nursing Home, Yinchuan, in January 2020. The results of the pilot study indicated that the FPS-R score of the control group and the intervention group was 5.97 ± 1.81 and 4.79 ± 1.96, respectively. We have consulted a statistician from the School of Medical Statistics and Epidemiology at Ningxia Medical University, who finished the randomization list of the recruits. With a type 1 error rate of 0.05 (*α* = 0.05, two-tail) and a 90% power (*β* = 0.10), the sample size of the study scheme was calculated by the statistical expert, which was 86 patients in each group. According to our study design and considering the particularity of this research subject (they are less likely to complete the entire experiment), we assume a 20% drop-out rate. The total sample size of 206 cases (per group was 103 cases) is required to reduce the underpower of the study.

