### Data statistical analysis

On the basis of the intention-to-treat (ITT) principle, SPSS version 22.0 (Chicago, IL, USA) will be recommended to run the data statistical analysis on both the real APP group and the sham APP group. Information on all patients in the random list should be included in the final analysis. If data is missing, the missing data imputation should be used to analyze the validity of the statistical analysis. The statistical description of categorical variables (the population demographic data) will be mainly presented by the relative number (rate, proportion, and ratio). The continuous variables (repeated measurement data of three physiological parameters) will be compared by analysis of variance (ANOVA) or the Kruskal-Wallis test (or chi-squared tests) for the two groups. Other categorical variables (data on satisfaction from caregiver, acceptance from patient, and additional use of analgesics) will be described by the nonparametric test (Wilcoxon’s rank sum test). A two-sided *P* value < 0.05 will be considered to be statistical significance. Therefore, subjects’ personal information, such as nationality, education, and medication history, will be used to consider whether to perform statistical analysis in subgroups.

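### Pain relief at T1 and at T2 is primary with no rule on whether one or both must succeed, and T1 is scored while pressing is still under way

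*Protocol article*

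**What the plan says.** All references are to the protocol article.

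- **Primary outcome measure:** "The level of pain relief at T1 and T2 will be considered as the primary outcome". The Abstract says the same. Neither place ranks the times or gives a success rule.
- **Data statistical analysis:** one general rule, that a two-sided P "value < 0.05 will be considered to be statistical significance". ANOVA or a rank test is assigned to the repeated physiological measurements. No test is named for the FPS-R.
- **Sample size estimation:** "With a type 1 error rate of 0.05", with "0.05, two-tail) and a 90% power". The basis is one pair of pilot values: "the FPS-R score of the control group and the intervention group was 5.97 ± 1.81 and 4.79 ± 1.96, respectively". Their time point is not given. The result is a number "which was 86 patients in each group".
- **Measurement:** scores are taken at baseline, then "at 5 min during performing the intervention (T1), and at 5 min after the intervention finished (T2".
- **Interventions:** "each auricular point will be pressed gently 2 times lasting 1 min each time", without pauses. The text announces four active points but lists three named points plus two for the pain site. The sham arm has five. Pressure in the true arm is meant to produce a painful swelling feeling, numbness and warmth; in the sham arm, warmth only.

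**The concern.** A superiority trial needs one answer to whether it succeeded. Here two results are primary and the protocol does not say how they combine. Without that rule, the stated 5% error rate and 90% power cannot both be attached to the trial's conclusion, and the choice between T1, T2, either or both could be made after the data are seen.

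The two times also measure different things. T1 falls during the stimulation and T2 after it has ended. The sensation sought during pressing differs between the arms and includes pain in the true arm only. Disagreement between T1 and T2 is therefore foreseeable, and the protocol has no answer for it.

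**Working it through.** **1. The plan's own sample size.** Inputs from Sample size estimation: means 5.97 and 4.79, SDs 1.81 and 1.96, two-sided alpha 0.05, power 90%.

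- Difference = 5.97 − 4.79 = 1.18.
- Mean variance = (1.81² + 1.96²)/2 = 3.559, so SD = 1.887.
- n per group = 2 × (1.960 + 1.282)² × 3.559 / 1.18² = 53.7, so 54 (55 by t-test).

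The stated 86 does not reproduce; that is a separate matter. What counts here is whether 86 contains a hidden allowance for two primary tests. With alpha split to 0.025 per test, 2 × (2.241 + 1.282)² × 3.559 / 1.18² = 63.4, so 64. An alpha split does not explain 86 either, and the section describes only one comparison.

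**2. If success at either time counts.** Each test is taken at two-sided 0.05 and the two statistics as bivariate normal with correlation r. The document gives no r, so a range is assumed.

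Family-wise error = 1 − P(|Z1| < 1.96 and |Z2| < 1.96). At r = 0 this is 1 − 0.95² = 9.75%.

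**3. If both times must succeed.** The error rate stays at or below 5%. With 90% power for each test, joint power = P(Z1 < 1.282 and Z2 < 1.282). At r = 0 this is 0.90² = 81%.

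| Assumed r | Error, either suffices | Joint power, both required |
|---|---|---|
| 0 | 9.75% | 81.0% |
| 0.5 | 9.1% | 83.2% |
| 0.7 | 8.3% | 84.7% |
| 0.8 | 7.8% | 85.6% |
| 0.9 | 7.0% | 86.9% |

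**4. How much slack 86 per group gives.** On the pilot inputs, 86 per group has 98.4% power at 0.05 and 96.9% at 0.025. If the pilot effect held at both times, joint power would be at least 0.984² = 96.8%. The 81% to 87% figures therefore apply to the design's stated 90%, not to the pilot effect taken at face value.

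**5. Where T1 falls.** Each point takes 2 × 1 = 2 min.

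- Five points as listed: 5 × 2 = 10 min, so T1 is at 5/10 = 50%.
- Four points as stated for the true arm: 4 × 2 = 8 min, so T1 is at 5/8 = 62.5%.

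On either count T1 is scored during pressing. T2 is not.

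**6. Direction of any procedural pain.** If ear pain from pressing enters the FPS-R rating, it raises the T1 score in the true arm and not in the sham arm. That works against showing benefit at T1.

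**The case against.** **The error inflation is inferred.** A reader might conclude that T1 and T2 are each tested at 0.05, that either can declare success, and that the false-positive rate therefore exceeds 5%. The text does not say so. It gives one general threshold and refers to a single outcome at two times, which could equally mean that both must be positive, or that one repeated-measures comparison is intended. This stands: the 7.0% to 9.75% range is conditional. Since the same patients rate the same scale minutes apart, 9.75% is an upper bound rather than a likely value. It does not remove the gap, because no reading is stated and the repeated-measures analysis is described only for the physiological parameters.

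**Multiplicity detail can be left to the SAP.** An adjustment method or a testing order can be. The protocol, however, does fix the primary outcome, and fixes it as two unranked times. That is a choice badly made rather than a detail left out.

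**The sensation difference.** A reader might take it as a further source of false positives. The documents do not support that: its likely direction is against the true arm. That ear pain enters the score at all is also an inference; the protocol describes gentle pressing within the patient's endurance and locates the target pain with the BPI-C. It is a reason to prefer T2, and no more.

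**T1 as the midpoint.** This holds only on the five points listed, not on the four stated.

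**T2 is not the only cure.** Requiring both times, or splitting alpha, would also work, and on the pilot inputs a split needs no more patients than are planned. Effect during treatment is a legitimate question. This also stands; what matters is that one rule is fixed in advance.

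**Conclusion.** The concern holds in conditional form. Two primary time points are fixed without a success rule, and the sample size is tied to neither of them.

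- If either time suffices and each is tested at 0.05, the family-wise error is 7.0% to 9.75%, for assumed correlations of 0.9 to 0.
- If both are required, the 5% level is kept and joint power is about 81% to 87% at 90% per test.

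The protocol does not determine which applies, so it cannot be said that the trial's error rate is in fact inflated. T1 is scored during pressing on either point count and may include procedural ear pain in the true arm, which would tend to mask benefit. This should be fixed. It does not make the trial unsound, because the repair is a matter of definition and the planned numbers leave room for it.

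**What to change.** Before unblinding, amend the protocol to:

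1. name FPS-R at T2 as the single primary endpoint, tested at two-sided 0.05;
2. make T1 the first secondary endpoint, tested at 0.05 only if T2 is significant (fixed sequence, so the overall error over the two tests stays at 5%);
3. describe T1 as the score during stimulation;
4. state which time point the pilot means and the sample size refer to;
5. reconcile the stated four active points with the five listed, since the position of T1 within the session depends on it.

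**Cost:** T1 loses co-primary status, and a benefit seen only at T1 could no longer be claimed as the primary result. No extra patients, measurements or changes to treatment are needed.
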